#### Maximising retention

To maximise the response rate, everyone who returns the accelerometer with valid data and a completed questionnaire will be entered in a prize draw to receive one of twenty £20 gift vouchers. Participants are also given a study ID card and pen at baseline to remind them of their involvement in the study. To ensure that timing is convenient to receive the accelerometer, participants are contacted (by text, telephone or email) 1 week before the accelerometer and questionnaire are mailed.

#### Data management/quality assurance

The randomisation sequence for the web-based randomisation tool has been generated independently of the study team. Electronic randomisation records will be checked against the CRF for fidelity.

The administrative database is managed in-house. The database has been designed to allow easy entry of CRF data and the short baseline questionnaire. Random checks are performed on the entered data against paper records, and all errors are logged and corrected.

Double data entry of the follow-up questionnaire will be done by an experienced independent agency. The resulting spreadsheets will be interrogated for invalid values and corrected. In addition, random checks will be applied as above.

The objective PA data is checked weekly for completeness, and participants are asked to wear the Actigraph monitor for extra days if the minimum wear time of 10 hours a day over a 3-day period has not been achieved.

The audio-recordings will be submitted to an independent transcription agency and stored on a secure drive on a University server.

We are promoting walking as a means of increasing PA, and the duration of the trial for participants is 3 months. Evidence from our previous trial suggested that the risk of harm or injury to a patient associated with our trial is low. We do not foresee any events or circumstances in which we would need to stop the trial prematurely. No interim analysis or stopping guidelines have been made prior to the study. However, a trial steering committee made up of an independent chair, three independent members, including members of the Public and Patient Involvement (PPI) panel, representatives from the funder and the sponsor, and three members of the research team will oversee all aspects of the trial.

Data analysis will be undertaken on completion of data collection, database lock and data cleaning.

#### Confidentiality

The research team will have no access to identifiable data prior to consent. Study invitations are sent directly from GP practices. The storage and movement of identifiable and sensitive data between GP practices and the research team will be undertaken following the guidelines and principles of Good Clinical Practice, the Data Protection Act 1998 and the NHS England confidentiality policy. The chief investigator will be the custodian of the trial data set, and only authorised personnel will have access to the (anonymous) data.

### Study outcomes

Data are collected by nurses and healthcare assistants during the NHS Health Check and from questionnaires and accelerometer wear at 3 months post-NHS Health Check. See Table 2 for a full list of outcome measures.

**Table 2 Tab2:** Study measures

	0 months	3 months
Accelerometer measures		
Activity counts per minute		X
Step counts per day		X
Time (minutes/day) in light/sedentary activity		X
Time (minutes/day) in moderate activity		X
Time (minutes/day) in vigorous activity		X
Time (minutes/day) in moderate or vigorous activity		X
Questionnaire measures		
Physical activity energy expenditure (PAEE) (kj/kg/day)		X
Home-based PAEE (kj/kg/day)		X
Work-based PAEE (kj/kg/day)		X
Leisure-based PAEE (kj/kg/day)		X
Commuting PAEE (kj/kg/day)		X
Screen/TV time (hours per day)		X
Gender	X	
Age (calculated from date of birth)	X	
Ethnicity	X	
Education	X	
Employment status	X	
Household income	X	
Marital status	X	
Home ownership	X	
Vehicle ownership	X	
Dependents	X	
Individual deprivation score	X	
Area deprivation score (Index of Multiple Deprivation, IMD, based on home postcode)	X	
Recall of physical activity (PA) advice		X
PA awareness		X
Use of intervention materials		X
Enactment of behaviour change techniques		X
Contamination of sample		X
Primary care visits		X
Hospital visits		X
Out of pocket expenditure		X
Work productivity		X
National Health Service (NHS) Health Checks		
10-year cardiovascular risk score (QRisk2)	X	
Activity level (Derived from GPPAQ)	X	
Duration of health check	X	
Nurse/Healthcare assistant delivery	X	
Physical activity referrals	X	

#### Primary outcome

The primary outcome is PA (total body movement) measured by tri-axial accelerometry (Actigraph GT3X+ or Actigraph w-GT3X-BT, ActiGraph, Pensacola, Florida, USA) expressed as average vector magnitude acceleration (counts per minute). Data collected at 60Hz will be integrated into 10-second epochs. Non-wear time, defined as strings of 90 minutes of consecutive zeros (on the vertical axis), will be excluded, and the remaining vector magnitude data will be summarised into average acceleration (counts per minute (cpm)).

#### Secondary outcomes

Secondary outcomes derived from the accelerometer data are step counts (average step counts per day) and the average number of minutes per day spent in sedentary/light activity (<2,690 cpm); moderate activity (2,690–6,166 cpm); vigorous activity (≥6,167 cpm); and moderate or vigorous activity (≥2,690 cpm) [22].

Self-reported PA outcome measures will be obtained using the validated Recent PA Questionnaire (RPAQ) [20]. Total Physical Activity Energy Expenditure (PAEE), domain-specific PAEE (home, work, leisure-time and commuting) and screen/TV viewing time over the past 4 weeks will be calculated using reported frequency and duration for each activity, together with estimated activity-specific metabolic cost [23].

The cost analysis will inform an economic evaluation and will comprise costs to participants, the NHS (including the cost of the intervention itself), and lost productivity. Costs to participants will be calculated from out-of-pocket expenditure reported in questionnaires, adjusted to the price year of the analysis using the consumer price index (CPI). The value of lost productivity will be calculated from the WPAI [21]. This estimates reduced productivity whilst at work (‘presenteeism’) as a self-assessed proportion of maximum productivity, as well as days absent from work. The cost will be calculated as the sum of whole-day equivalents of work lost multiplied by the median daily wage in England rate for the price year of the analysis. The cost to the NHS will be calculated as the sum of self-reported primary and secondary care contacts multiplied by representative unit costs pertaining to the price year of the analysis (e.g. NHS Reference Costs [24] and Curtis [25]). Finally, the cost to the NHS of providing the intervention will be calculated from study records of expenditure on pedometers, materials and training and the time required to deliver the VBI.

#### Process measures

The process evaluation is informed by recent Medical Research Council guidance [26] and will focus on the mechanisms underlying any intervention effects and the implementation (fidelity of delivery) of intervention and control consultations.

##### Mechanisms of impact

Variables hypothesised to be on the causal pathway of any effects include (1) recall of any PA advice received during the NHS Health Check consultation (two items); (2) awareness of PA recommendations and own PA levels (two items); (3) the use of any materials handed out (e.g. booklet; three items); and (4) enactment of key behaviour change techniques included in the intervention (e.g. goal setting (behaviour) and self-monitoring (behaviour); four items).

##### Fidelity of delivery

A reliable coding frame will be developed and piloted for inter-rater reliability to assess the following variables: (1) duration of the NHS Health Check and the intervention (if applicable); (2) delivery of the standard NHS Health Check (e.g. taking a blood sample or measuring blood pressure); (3) delivery of the intervention (e.g. feedback on PA levels, mention PA recommendations, explain the pedometer, prompt goal setting and self-monitoring, and give a booklet); and (4) contamination, by coding of any intervention-related components in the control consultations.

### Sample size

A trial of 394 participants per arm followed up is sufficient to detect a 0.2 sd (‘small’) difference in mean activity between arms (40 accelerometer cpm) based on the standard deviation of 200 cpm estimated in the previous trial) with 80 % power. However, allowing for attrition of 30 % at follow-up (i.e. 30 % of participants not providing sufficient accelerometer data), an initial sample size of 570 per arm would give 80 % power to detect an effect of this size between the two conditions (alpha = 0.05, two-sided test).

Recruitment and attrition will be monitored. If attrition is lower than 30 % and we anticipate achieving follow-up of 394 participants per arm with sufficient accelerometer data from randomising fewer than 570 per arm, participant recruitment will be closed.

### Statistical analyses

Full details of the statistical methods are provided in the statistical analysis plan. The following is a summary of the main analyses proposed.

We will use analysis of covariance to test for intervention effects on continuous outcomes and quantify these with differences in means and 95 % confidence intervals, adjusting for primary care practice, gender and age. Logistic regression will be used for binary outcomes. An intention-to-treat approach will be used, supported by a per protocol analysis for the primary outcome analysis. All significance tests will be two-sided and assessed at the 5 % level of significance.

Missing data in the primary outcome will be handled within a sensitivity analysis considering optimistic and pessimistic scenarios for the intervention effect size in those with missing data and incorporating baseline predictors of primary outcome missing status that are differential by group. This analysis will be undertaken to examine the robustness of the main analysis result to the ‘missing at random’ (MAR) assumption. The aim is to adequately explore the impact of departures from the MAR assumption on the primary outcome results [27].

Pre-specified subgroup variables will be examined in relation to the primary outcome and will involve an initial test of differential intervention effect across the subgroup variable before summarising the intervention effect within the subgroup categories. These subgroup variables will include baseline cardiovascular risk, gender, age (40–59; 60–74 years), ethnic group, educational qualifications, employment status, household income, marital status, home ownership, vehicle ownership, and deprivation score (Index of Multiple Deprivation (IMD) 2007, derived from the participant’s home postcode [28]). For a continuous moderator such as CVD risk, the intervention effect observed in the highest tertile of the moderator will be estimated with a 95 % confidence interval having an informative width of +/- 25 thousand activity counts per day.

Incremental effectiveness will also be formally integrated with incremental cost data forming a within-trial economic evaluation. This will estimate the incremental cost per incremental MET(Metabolic Equivalent of Task)-hour of physical activity gained (estimated from accelerometer counts). The analysis will be reported from the perspectives of the NHS and society. Current guidelines on the conduct and reporting of economic evaluations will be followed [29–31]. Analysis of uncertainty will comprise the estimation of 95 % confidence intervals around incremental costs and outcomes and construction of the cost-effectiveness acceptability curves.

In addition to the within-trial analysis, results will be combined with prior data on the costs and effects of the intervention, and a previously developed model will be updated with the new evidence to predict the longer-term costs and outcomes associated with the intervention and control. This will yield a revised estimate of the incremental cost per QALY gained. The revised decision uncertainty will be reported as an updated cost-effectiveness acceptability curve.

Questionnaire measures relating to the proposed mechanisms of impact of the intervention (recall of PA advice, awareness of PA, use of intervention materials, and enactment of behaviour change techniques) will be analysed descriptively. Variables that assess fidelity of the intervention and control consultations, derived from coding the audio-recordings, will also be analysed descriptively. Two overall fidelity scores will be calculated, expressed as the number of components delivered out of those that should be delivered for (1) the NHS Health Check (intervention and control consultations) and (2) the intervention (intervention consultations only).

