#### The NHS Health Check

Healthcare assistants and nurses conducting the NHS Health Checks obtain informed consent from participants following Good Clinical Practice guidelines [18]. Once consent has been given, participants are asked to complete a short questionnaire. The information provided in this questionnaire will be used to characterise the sample and check baseline comparability between arms. The healthcare practitioner accesses the web-based randomisation tool at this time to determine to which intervention arm the participant has been assigned. The rest of the consultation proceeds following the usual NHS Health Check procedures, and the Step It Up intervention is delivered at the end to participants in the intervention arm.

Healthcare practitioners also complete a CRF, which is a written record of the consultation. It is intended as a guide and provides prompts for each stage of the consultation. One additional piece of information is collected: the baseline PA level. This measure is derived during the NHS Health Check using the GP PA Questionnaire (GPPAQ) [19] and is used as the basis for individual feedback at the start of the Step it Up intervention as well as providing a baseline measure of PA. The questionnaire asks about the patient’s PA at work and leisure time in the past week.

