After careful consideration, we decided not to measure the primary outcome at baseline. A baseline measure would have a number of advantages: sample size could be reduced, and an analysis of individual change scores would be possible. However, pilot work undertaken in preparation for this trial identified two potential problems arising from objective measurement of PA at baseline. First, baseline measurement is logistically difficult and may compromise uptake of the NHS Health Check and the flow of participants through the trial. Second, baseline accelerometry could act as an intervention; that is, some participants may increase their activity as a result of wearing the device, leaving less scope for our very brief intervention to have an effect [33].

The Step It Up intervention was chosen after a rigorous selection process [10] and evaluation in a previous trial (Pears S, Bijker M, Morton K, Vasconcelos J, Parker RA, Westgate K, et al.: A randomised controlled trial of three very brief interventions for physical activity in primary care, submitted) (ISRCTN02863077). The intervention is well characterised in terms of the component BCTs, is feasible to deliver in practice with limited training and is acceptable to both practitioners and participants. External validity is further increased by using nurses and healthcare assistants already trained to carry out NHS Health Checks.

The trial team brings together expertise in behavioural science, intervention development and evaluation, measurement of PA, medical statistics, health economics, and the design, conduct and analysis of primary care trials. In designing this trial, we have drawn on our previous work and on the guidelines and principles of trial reporting laid out in SPIRIT [34] and CONSORT [35]. See Additional file 1 for the SPIRIT Checklist.

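### The primary ANCOVA makes no use of the GPPAQ activity level collected at 0 months: lost efficiency, recoverable only if the GPPAQ is recorded before allocation is disclosed

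*Protocol article*

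**What the plan says.** The Statistical analyses section of the protocol article specifies analysis of covariance for continuous outcomes, "adjusting for primary care practice, gender and age". The section calls itself a summary and refers to the analysis plan for detail, but it does name the covariates.

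Under The NHS Health Check, the GPPAQ activity level serves as the basis for individual feedback in Step It Up, "as well as providing a baseline measure of PA". Table 2 (Study outcomes) marks it at 0 months with no restriction to one arm. It is neither among the covariates nor among the subgroup variables listed.

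The Discussion explains why the accelerometer is not worn at baseline and concedes the price: "A baseline measure would have a number of advantages: sample size could be reduced". It gives two reasons: baseline wear is logistically hard and could reduce uptake, and wearing the device could itself change behaviour.

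On timing, the Abstract places random allocation at the start of the Health Check. The Randomisation section says practitioner and participant are blind only until the web tool is used, after which the participant is told the arm. The NHS Health Check section gives the order as consent, short questionnaire, randomisation tool, then the rest of the check. It says the GPPAQ is derived during the check.

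**The concern.** Baseline activity is the most obvious prognostic factor for activity three months later. A covariate that explains outcome variance narrows the confidence interval without further recruitment and corrects chance imbalance in that covariate. Neither of the Discussion's reasons for omitting baseline accelerometry applies to a short questionnaire that is completed anyway, and the article does not consider it as a partial substitute.

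The trial has no spare precision. It is sized at 80% power, and the Sample size section closes recruitment early if 394 per arm with sufficient data are expected from fewer randomised. Good retention therefore shortens recruitment and does not add power.

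Missing data give a further, weaker reason. The protocol allows for 30% of participants without sufficient accelerometer data. If baseline activity predicts both valid wear and later counts, a main analysis that conditions on it rests on a more credible missing-at-random assumption.

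**Working it through.** **Inputs from the Sample size section.** Target: "difference in mean activity between arms (40 accelerometer cpm"). Variability: "standard deviation of 200 cpm estimated in the previous trial". Test: "alpha = 0.05, two-sided test". Followed up: "A trial of 394 participants per arm followed up is sufficient". Randomised: "an initial sample size of 570 per arm would give 80 % power".

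**Step 1: reproduce the plan's figure.**
n per arm = 2 × (1.96 + 0.8416)² × 200² / 40² = 2 × 7.849 × 25 = 392.4, so 393. The noncentral t distribution gives 394, as stated.
Inflation for attrition: 394 / 0.70 = 563, against 570 stated (570 × 0.70 = 399 followed up). The plan's figure is slightly generous.
Power at 394 per arm: SE = 200 × √(2/394) = 14.25 cpm; 40 / 14.25 = 2.807; Φ(2.807 − 1.96) = 0.802.
The SD of 200 carries no reduction for any covariate, so the stated power does not depend on adjustment.

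**Step 2: add the GPPAQ.** Let r be the partial correlation of the GPPAQ with 3-month cpm, given practice, gender and age. The documents do not give r, so the range below is an assumption. The SD of 200 is taken as the residual SD before the GPPAQ enters. Then

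residual SD = 200 × √(1 − r²); power = Φ(40 / [SD × √(2/394)] − 1.96).

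Example for r = 0.3: SD = 200 × √0.91 = 190.8; SE = 13.59; 40 / 13.59 = 2.943; Φ(0.983) = 0.837.

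| Assumed r | Residual SD (cpm) | SE smaller by | 95% CI half-width (cpm) | Power at 394 per arm | n per arm for 80% |
|---|---|---|---|---|---|
| 0 | 200.0 | – | 27.9 | 80.2% | 393 |
| 0.1 | 199.0 | 0.5% | 27.8 | 80.5% | 389 |
| 0.2 | 196.0 | 2.0% | 27.4 | 81.7% | 377 |
| 0.3 | 190.8 | 4.6% | 26.6 | 83.7% | 358 |
| 0.4 | 183.3 | 8.3% | 25.6 | 86.5% | 330 |
| 0.5 | 173.2 | 13.4% | 24.2 | 90.0% | 295 |

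In terms of sample size, the factor 1/(1 − r²) is 1.01, 1.04, 1.10 and 1.19 for r = 0.1 to 0.4. Adjustment is then worth 1%, 4%, 10% or 19% more participants followed up.

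**Step 3: check whether the GPPAQ precedes allocation.** Read together, the Abstract, the Randomisation section and The NHS Health Check section put randomisation and disclosure early in the consultation and the GPPAQ later, within the check itself. Step It Up comes at the end. On this order the GPPAQ precedes the intervention but follows disclosure of the arm. The article implies this order but does not state it outright.

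**The case against.** The strongest case against acting is that nothing in the stated model is wrong. Practice is the stratification factor, the model is valid under randomisation, and the sample size already delivers 80% power without the GPPAQ. A further covariate is a matter of efficiency. That stands, and it limits the point.

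The timing objection also stands. On the described order the GPPAQ is a self-report, taken by a practitioner and from a participant who both know the arm. If that knowledge shifts the answers, adjusting the primary estimate for them could introduce bias. Leaving the GPPAQ out of the primary model is then defensible. A reader might infer that it can go straight into the model as an ordinary baseline covariate. The documents do not support that until its timing is settled.

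The size is uncertain. The relevant r is partial, the GPPAQ covers only the past week, and the Background itself warns of recall and social desirability bias in self-reports. A value near 0.1, with almost no gain, is as compatible with the documents as 0.4.

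The missing-data argument is plausible but undocumented: nothing says the GPPAQ predicts valid wear. The planned sensitivity analysis already admits baseline predictors of missingness that differ by arm, and the GPPAQ could qualify. That does not reach the main model.

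Finally, the unseen analysis plan may add adjusted models. The article nonetheless commits to a specific covariate set, so the omission can be raised against what it states.

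**Conclusion.** The point holds as a modest, avoidable loss of efficiency. The article collects a baseline activity measure in both arms, concedes the value of having one, and leaves it out of the main model. The omission itself is certain on the text. The benefit depends on an assumed correlation: from r = 0.1 to 0.3 the standard error falls by 0.5% to 4.6% and power rises by about 0.4 to 3.6 percentage points. Only towards r = 0.4 to 0.5 does the gain become substantial.

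A reader might go further and infer that the primary estimate is biased, that the trial is underpowered, or that the missing-at-random assumption fails. The documents support none of these. Randomisation protects the estimate when data are complete, the power calculation reproduces without covariates, and no evidence links the GPPAQ to missing outcomes.

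**What to change.** 1. State when the GPPAQ is completed relative to allocation. From now on, complete it with the short questionnaire before the randomisation tool is opened.
2. Before unblinding, pre-specify the GPPAQ activity level as a categorical covariate in the primary ANCOVA, in the ANCOVAs for the other physical activity outcomes and in the missing-data model, provided it is confirmed to have been recorded before allocation was disclosed.
3. If it was recorded after disclosure, as the described order implies for participants already recruited, keep the stated model as primary and pre-specify the GPPAQ-adjusted model as a sensitivity analysis.
4. Prognostic variables from the pre-randomisation short questionnaire can enter the primary model without that condition.

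The analysis change needs no new data or participants. Reordering is a small change to the consultation, but recruitment is underway in 23 practices, so the case report form and practitioner instructions would need updating. A few GPPAQ values will be missing, and their handling should be fixed in advance, for example by a missing category. The main risk is bias if answers given after disclosure enter the primary model, which step 3 avoids.

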Participants will also be asked to complete a questionnaire once they have finished wearing the accelerometer. The questionnaire consists of three parts:*Recent physical activity questionnaire (RPAQ)*. Self-reported PA over the previous 4 weeks is measured across four domains (home, work, travel and recreation). Section A on home activities asks questions on the frequency of television viewing, computer use and stair climbing. Section B asks questions about the type of work and the time spent there, as well as assessing the mode of travel to and from place of work. The final section asks about the frequency and duration of frequently performed recreational activities. When tested against two gold standard methods of obtaining PA energy expenditure (PAEE) (doubly labelled water and combined heartrate and movement sensing), the RPAQ has been shown to be a valid tool for ranking individuals according to PAEE [20].*NHS use, workplace productivity and expenditure on PA questionnaire*. A bespoke questionnaire on primary and secondary care contacts and expenditure on health, sports clubs or other physical activities was developed and piloted prior to the trial. Work place productivity is based on an adapted version of the validated Work Productivity and Activity Impairment (WPAI) Questionnaire [21].*Process evaluation*. (1) For mechanisms of impact, a series of questions is used to assess whether the intervention and materials were received by participants during the NHS Health Check and subsequently used, and (2) for contamination, participants are asked if they know anyone else who has taken part in the study, and if yes, whether they were in the intervention or control group.

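### Work-based and commuting energy expenditure are adjusted only for practice, gender and age; adding baseline employment status, already recorded, would tighten these two secondary estimates

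*Protocol article*

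**What the plan says.** Under Secondary outcomes, the protocol article lists total PAEE and "domain-specific PAEE (home, work, leisure-time and commuting"). These scores "will be calculated using reported frequency and duration for each activity, together with estimated activity-specific metabolic cost". The Follow-up section describes the source questionnaire: "Section B asks questions about the type of work and the time spent there", together with how people travel to and from work. Table 2 places all PAEE measures at 3 months only, so none has a baseline value.

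The Statistical analyses section states one model: "We will use analysis of covariance to test for intervention effects on continuous outcomes", "adjusting for primary care practice, gender and age". On the analysis population it says "An intention-to-treat approach will be used, supported by a per protocol analysis for the primary outcome analysis".

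"Employment status" appears in Table 2 at 0 months. It has two stated uses. As part of the baseline questionnaire it describes the sample and checks comparability between arms (The NHS Health Check section). It is also one of the pre-specified subgroup variables for the primary outcome.

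**The concern.** Eligible patients are aged 40 to 74, a range that spans usual retirement age, so a sizeable share may have no job. Someone with no workplace has no working hours and no commute to report, and a score built from frequency and duration would then be zero. Baseline employment status would thus largely determine whether either outcome can exceed zero. Age and gender are only partial proxies for it.

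With no baseline value of these outcomes to adjust for, employment status is a strong candidate covariate. Leaving it out keeps the gap between workers and non-workers in the residual variance and widens the confidence intervals. The Discussion justifies the self-report measures by what they add on the type and pattern of activity, and the domain scores serve that purpose. What is at stake is how sharply the work and commuting domains can be estimated. The primary accelerometer comparison is not at stake.

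**Working it through.** **The plan's own figure.** The sample size is for the primary outcome: difference 40 cpm, SD 200 cpm, two-sided alpha 0.05, power 80 %. Per arm, n = 2 × (1.960 + 0.842)² × (200/40)² ≈ 393, against 394 stated; power at 394 is 0.802. For 30 % attrition, 394/0.70 = 563, against 570 stated (570 × 0.70 = 399). The figure reproduces and this point does not alter it. No precision figure is stated for work-based or commuting PAEE.

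**Inputs for this point.** From the article: the covariate set, the 3-month-only measurement, employment status at 0 months, ages 40–74 and 394 followed up per arm. Assumed, because the article does not give them: p, the share in work; c, the SD/mean of the outcome among workers; and a score of zero for people without a job.

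**Formula without other covariates.** Let the outcome be 0 with probability 1 − p, and have mean μ and SD cμ among workers.

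- Variance within work-status groups: p c² μ²
- Variance between the groups: p(1 − p) μ²
- Share explained by work status: R² = (1 − p) / ((1 − p) + c²)
- Narrowing of the interval: 1 − √(1 − R²)

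For p = 0.7 and c = 1: R² = 0.3/1.3 = 0.231, and the narrowing is 1 − √0.769 = 12 %. At the same p it is 33 % for c = 0.5, 6 % for c = 1.5 and 4 % for c = 2. Over p = 0.5 to 0.9 and c = 0.5 to 2, it runs from 42 % down to 1 %.

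**With age and gender already in the model.** Simulation of 400,000 people per scenario: age uniform on 40–75, employment dropping at age 60, and a log-normal outcome among workers. Each entry is the further narrowing from adding work status.

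| In work under 60 / 60 and over | Overall share in work | c = 0.5 | c = 1 | c = 1.5 | c = 2 |
|---|---|---|---|---|---|
| 0.90 / 0.20 | 60 % | 29.5 % | 10.7 % | 5.0 % | 3.0 % |
| 0.85 / 0.35 | 64 % | 32.1 % | 12.0 % | 5.7 % | 3.3 % |
| 0.80 / 0.50 | 67 % | 32.9 % | 12.6 % | 6.1 % | 3.9 % |

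Example, middle row, c = 1: the residual SD falls from 0.914 to 0.804, and 1 − 0.804/0.914 = 12.0 %. Practice was not simulated.

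**Commuting.** Many workers may not commute actively, which raises c. Suppose 30 % of workers do, with SD/mean 0.6 among them. Then c² = (1 + 0.36)/0.30 − 1 = 3.53, so c ≈ 1.9. With p = 0.6, R² = 0.4/(0.4 + 3.53) = 0.102 and the narrowing is about 5 %, before age adjustment.

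**Validity.** With 394 per arm, structural zeros, c = 1, no true effect and adjustment for age and gender only, 2,000 simulated trials rejected in 5.75 %. The Monte Carlo standard error is √(0.05 × 0.95/2000) ≈ 0.5 %, so this is consistent with the nominal 5 %.

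**The case against.** The strongest reply is that the section describes itself so: "The following is a summary of the main analyses proposed". Scoring rules and covariates for individual secondary outcomes often sit in the SAP, which is not shown. This stands for the scoring rule: its absence from an article is no fault. It does not dispose of the covariate set, which the article states for continuous outcomes without exception. The SAP may nevertheless already add employment status.

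A common covariate set is also a defensible choice, and nothing about it is invalid. That stands, and it limits the point to efficiency.

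Four stronger readings are tempting, and the article does not support them:

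- *Employment status goes unused.* It is a baseline descriptor and a subgroup variable for the primary outcome. It is missing only from the adjustment of these outcomes.
- *The comparison is biased, or rests on a subset formed after randomisation.* Analysing everyone by randomised arm is unbiased. A post-randomisation subset would arise only if people without a job at 3 months were set to missing, and the article does not say so.
- *The covariate would cure dilution by people who cannot show an effect.* It would not. Adjusted or not, the linear model estimates the average over everyone. With 60–67 % in work and an effect only in workers, that average is 60–67 % of the workers' effect.
- *The same holds for lost-productivity cost.* The article states no covariate set for the cost analysis, so there is no stated rule to criticise.

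**Conclusion.** The point holds as a low-severity matter of precision on two secondary self-report outcomes. The stated covariates omit a recorded baseline variable that probably explains much of whether these outcomes are zero.

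The gain depends on how variable PAEE is among workers. It is substantial only if that spread is small (SD/mean near 0.5), moderate at 1.0 and slight at 1.5–2.0, where commuting probably lies. These sizes rest on an assumed 60–67 % in work, zero scoring for people without a job, and the simulated age patterns. The real gain would be somewhat smaller for two reasons: baseline status only approximates job status during the four-week recall at 3 months, and practice adjustment may already capture part of the difference.

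**What to change.** In the analysis plan, add baseline employment status (in paid work, yes or no) to practice, gender and age in the ANCOVA for work-based and commuting PAEE. Keep all randomised participants with follow-up data, and state that those without a job score zero on these two domains.

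Optionally, report as a supplementary analysis the effect among participants in work at baseline. This answers the separate question about workers that the covariate cannot answer. Do not define that group by work status at 3 months, which is observed after randomisation.

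The cost is a sentence or two and one degree of freedom in a model with about 788 followed up (2 × 394). No new data are needed. If the SAP already contains this, nothing has to change.
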